## Abstract

**Introduction:**

Cystic lesions of the pancreas have continued to present a clinical challenge for the past decades now. The increasing rate of detection, the lack of high-quality data on the natural biology of pancreatic cysts and the resulting difficulty to predict malignant transformation in different types of pancreatic cysts make patients with these diseases hard to manage. The German Pancreas Club Cyst Registry (GerPaCyst) (DRKS00025927) aims to establish a platform to discover and survey the natural and specific biology of pancreatic cysts such as IPMNs (main and branch ducts), SCNs, SPPT and MCNs, in a multicenter manner.

**Materials and methods:**

This manuscript is written according to the SPIRIT guidelines (See S2 and S3 Tables). Ethical approval was obtained from the University of Luebeck (2020-20-225) and all participating centers. In GerPaCyst patients aged ≥18 years with a pancreatic cyst under surveillance or scheduled for surgery should be enrolled. Participating centers will complete an electronic Case Report Form (eCRF) via REDCap which is designed as a longitudinal study minimizing the input of repeated measures. Changes in patient baseline data, cyst characteristics, both endoscopic and imaging data will be entered typically every 6–12 months during patient follow-up. Biobanking will be performed, when available. Duration of observation per patient is up to a maximum of 20 years or until end of follow-up or death.

**Results:**

The primary goal is to assess and calculate individual risk models for malignancy/high-grade dysplasia based on the collected clinical, molecular and imaging data (multi-omics prediction models) for each included cyst entity, therefore the primary outcome of this trial is the development of high-grade dysplasia/invasive cancer during follow-up or the absence of it. The secondary outcomes are death, quality of life measured by EQ-5D-5L questionnaire, end-of-follow up and perioperative characteristics, if applicable such as complications, length of hospital stay and clavien-dindo classification. Another goal will be to build a multicenter, interdisciplinary database to generate high-quality cyst biology data, which can then be used for further research questions. Additionally, this database will be utilized for registry- based interventional trials in the future.

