**These are the inclusion and exclusion criteria:**

**Inclusion criteria:**
Presumed pancreatic cyst of the following entities (IPMN, MCN, SPPT, SCN)At least 18 years old

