### Assessment of data

After browser-based data entry, the data are automatically checked for completeness and internal plausibility by software-based internal rules. Missing or implausible items create warning messages. The data is usually entered after seeing the patient in the outpatient clinic of the respective institution. Missing data will be handled according to the intended analysis. There is currently no external monitoring for the GerPaCyst Registry. Data are collected prospectively via standardized physician-completed questionnaires. Diagnosis will be made according to the standardized criteria outlines in the aforementioned guidelines. Regular quality control is performed by semiannual study meetings of the entire study group. Through these periodic audits harmonized data collection is ensured, combined with the use of the electronic database that automatically identifies and flags incomplete case forms. The GerPaCyst steering committee recognizes that some methodological aspects may require refinement during implementation. Any such changes will be documented and reported. Specifically, laboratory analyses and parameters used in risk models, as well as imaging parameters, may be subject to change over the course of the study.

For building a multi-omics risk stratification model for pancreatic cyst progression, we will utilize deep learning methods. First, we will ensure data processing and integration and preprocess data by normalization (proteomics, genomics, metabolomics, etc.) and harmonization. Data will further be integrated by feature selection and dimensions will be reduced. Then deep learning will be integrated such as neuronal networks. These calculations will be performed by designated bioinformaticians.

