### Statistics

The data required for the respective research question are compiled into an anonymized project-specific evaluation data set with special consideration of the resulting re-identification risk, if any, and made available for the research project. The GerPaCyst study group decides on the provision of the evaluation data sets for scientific evaluation.

For the development of risk models, we aim to utilize neuronal networks with elastic-net regression using R. ROC-Curves will be built for candidate risk variables. According to our and the experience of others, sample size should be ten to 20 times higher than the number of trainable parameters. As of now, we are planning to include 157 variables plus imaging and biomarker profiles (about 40 different parameters). Our sample size should therefore be at least 4000 patients (200x20). To achieve adequate participant enrolment, this study was set up as an international multicenter study. Descriptive data will be evaluated with R or SPSS according to the data characteristics. Nominal data will be evaluated with frequencies and percentages and differences with Chi-square test or the Kaplan-Meyer methods if pertaining to survival. Continuous data will be evaluated by median and interquartile range, differences between two groups will be calculated by Mann-Whitney U Test. Kaplan-Meyer approximation will be used for survival analyses. P-value will be set at p < 0.05.

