### Trial status

11 university hospitals throughout Germany are currently participating in this study. The first patient was entered in December 2021 and the study is ongoing. It is an interdisciplinary cooperation of surgeons. radiologists and gastroenterologists. At least 5000 patients are planned to be recruited from gastroenterology and surgical departments. Baseline characteristics such as metabolic/endocrine diseases, risk factors and family history, as well as pancreatic cyst data including MPD diameter, enhanced mural nodules, calcifications and the quality-of-life EQ-5 questionnaire will be assessed during index visit and follow-up. Biospecimens like blood, cyst fluid and cyst cytology will be collected, if needed.

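### The primary goal promises a risk model for each cyst entity, but the 4000 patients are derived for one model of about 200 parameters

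*Protocol article*

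**What the plan says.** The Abstract (Results) gives the primary goal as "individual risk models for malignancy/high-grade dysplasia based on the collected clinical, molecular and imaging data (multi-omics prediction models) for each included cyst entity". The inclusion criteria name the entities: "Presumed pancreatic cyst of the following entities (IPMN, MCN, SPPT, SCN". The Abstract (Introduction) also separates the two duct types of IPMN: "IPMNs (main and branch ducts), SCNs, SPPT and MCNs".

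The Statistics section gives the rule, "sample size should be ten to 20 times higher than the number of trainable parameters", and then the inputs, "we are planning to include 157 variables plus imaging and biomarker profiles (about 40 different parameters". It concludes: "Our sample size should therefore be at least 4000 patients (200x20". It contains no term for the number of entities and no target per entity. Trial status gives a total for the whole registry: "At least 5000 patients are planned to be recruited from gastroenterology and surgical departments".

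The number of models differs between sections. The Statistics section uses the plural. Assessment of data, and the paragraph on central imaging review under Participants, eligibility criteria and outcomes, each refer to a single risk stratification model. Assessment of data also says: "Data will further be integrated by feature selection and dimensions will be reduced". It does not say to how many parameters.

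**The concern.** A model fitted separately for an entity learns only from patients with that entity. A total that just satisfies a patients-per-parameter rule for one model cannot satisfy the same rule for four models of that size once the patients are divided among them. The goal in the Abstract and the calculation in Statistics therefore describe different analyses.

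This concerns the primary goal, and the product is a malignancy risk for an individual patient. If entity-specific models are later published on the strength of the 4000, readers will take them to meet the registry's own sample-size standard. For at least two of the four entities, a model of the stated size would not meet even the lower end of it.

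**Working it through.** **Inputs, all from the protocol article**
- Parameters: 157 + about 40 = 197, rounded to 200 (Statistics).
- Rule: 10 to 20 patients per trainable parameter (Statistics).
- Totals: at least 4000 (Statistics); at least 5000 (Trial status).
- Entities: 4 (inclusion criteria). Counting main-duct and branch-duct IPMN as two models, which is my assumption, gives 5.
- Entity mix: not given.

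**1. Reproduce the plan's figure.** Patients per model = multiplier × parameters.
- 20 × 200 = 4000, as stated (20 × 197 = 3,940).
- 10 × 200 = 2000 at the lower end (10 × 197 = 1,970).

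The 4000 is thus the upper end of the rule applied to one model. It cannot be a per-entity figure, because the whole registry is planned at 5000 or more.

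**2. How many full-size entity models meet the rule?** Number = total ÷ patients per model, rounded down.

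| Total | 20-fold | 10-fold |
|---|---|---|
| 4000 | 4000/4000 = 1 | 4000/2000 = 2 |
| 5000 | 5000/4000 = 1.25, so 1 | 5000/2000 = 2.5, so 2 |

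These are upper limits for any case mix. At 4000, one entity reaches 20-fold only if it makes up the whole cohort, and two reach 10-fold only if each is exactly half. At 5000 the required shares are 80% (4000/5000) and 40% each (2000/5000). With 197 parameters instead of 200 the counts remain one and two.

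**3. Total needed for every entity.**
- Four models: 4 × 2000 = 8,000 (10-fold) to 4 × 4000 = 16,000 (20-fold). With 197 parameters: 7,880 to 15,760.
- Five models: 10,000 to 20,000.

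**4. Illustration with an even split.** This is an assumption.
- 4000/4 = 1000 per entity, and 1000/200 = 5 patients per parameter, half of the rule's lower limit.
- 5000/4 = 1250 per entity, and 1250/200 = 6.25.
- Turned round, 1000 patients support 1000/20 = 50 to 1000/10 = 100 parameters per entity model, not 200.

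**The case against.** **The goal may mean one model that covers every entity.** The wording in the Abstract can be read as individual-level risk across all entities, and two places in the Methods use the singular. A pooled model may therefore already be intended. That stands as a possible reading, and a reader who infers that the sample size simply fails goes too far. It does not remove the point: the Abstract says each entity, Statistics uses the plural, and nothing in the article settles which is meant.

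**Dimension reduction is planned, and elastic-net is named.** Either could bring an entity model down to the 50 to 100 parameters of the illustration. But no reduced count is given, and the 4000 was built on the unreduced 200.

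**The totals are minimums.** Both are worded as floors, and the registry is open to new centres. The limits of one and two entities therefore apply at the stated totals and are not a ceiling on what the registry may reach. The article gives no target near 8,000.

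**Details may be in the full protocol or a later SAP.** Per-entity planning may exist there. The point is not that it is missing here, but that two statements in the article do not fit together.

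**Stronger readings that the article does not support.**
- A reader might convert the patient numbers into events per entity using the risks in the Introduction. Those (3.7% overall, 7.8% and 25% at 10 years for low- and high-risk lesions) are for IPMN only and count cancer, whereas the primary outcome also counts high-grade dysplasia.
- A reader might say that rarer entities will have only very small samples, or that their risk estimates will be worthless. No entity mix is given, and neither claim can be shown from the article.
- The rule is a rule of thumb. The article states no precision target that could be missed.

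**Conclusion.** The point holds as an inconsistency between the primary goal and the sample-size statement. The conclusion about full-size entity models rests on two premises: that each entity gets its own model, and that each model keeps about 200 parameters. It does not depend on the case mix, on 197 versus 200 parameters, or on 4000 versus 5000 patients.

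That the 4000 belongs to one pooled model is an inference. The article does not use the word, but the single multiplication and the registry total leave no other consistent reading.

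The calculation also counts input variables as trainable parameters. A neural network normally has more weights than inputs, so the shortfall shown here is, if anything, on the low side.

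**What to change.** Reconcile the Abstract (Results), the imaging-review paragraph under Participants, eligibility criteria and outcomes, Assessment of data, and Statistics. No further enrolment is needed for this. I would write:

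1. The 4000 refers to one pooled penalised model with presumed entity at baseline as a predictor and shrunken entity-by-predictor interactions.
2. Calibration is reported separately for each entity.
3. A separate entity model is fitted only where a pre-set number of high-grade dysplasia or cancer events is reached. Its parameter count is limited to what that entity's data support and is stated after feature selection.

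If the steering committee prefers to keep separate models as the primary goal, giving a sample size and a reduced parameter count for each entity would also remove the contradiction.

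The cost is wording, with data collection unchanged. The scientific price is a reduced claim for rarer entities and predictor effects that are partly shared across entities.

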**Discussion:**

GerPaCyst will provide a valuable platform for clinical outcomes research. Fundamental factors affecting the development of pancreatic cysts over time will be identified. New research questions might be answered during the study period and will be made available through continuous publications.

**Trial registration:**

The study was prospectively registered at the German Clinical Trial Register (DRKS) under DRKS00025927 on September 14^th^, 2021, before inclusion of the first patient. The Universal Trial Number (UTN) is U1111-1302–9822.

## Introduction

Cystic lesions of the pancreas can either be neoplastic or non-neoplastic. Neoplastic cystic lesions include intraductal mucinous papillary neoplasms (IPMN), mucinous cystic neoplasms (MCN), serous cystic neoplasms (SCN) and solid pseudopapillary tumors (SPPT) and make up 90% of all neoplastic cystic tumors of the pancreas [1]. Depending on the entity, pancreatic cysts bear malignant potential that is associated with outcomes comparable to pancreatic cancer [2].

However, diagnostic accuracy remains limited [3]. The accuracy of cross-sectional imaging varies between 39.5% and 46%.

Pancreatic cysts occur in up to 45% in the German population [4]. The incidence is roughly 13% in Germany and the management of pancreatic cysts has therefore become a highly relevant clinical issue. Recent improvements in high-resolution imaging that make their detection more frequent stands in contrast to treatment algorithms that remain highly controversial in the absence of high- quality controlled studies. Between 2012 and 2018 international guidelines for the treatment of pancreas cysts were published [5–8]. All these guidelines make different recommendations on surveillance of small cysts after five years [9].

However, most of these recommendations are under the bias of retrospective surgical series and observational studies [10,11]. Thus, they probably overestimate the potential for malignancy. Analyses that go beyond five or even ten years hardly exist, which makes it difficult to predict the biology of these entities [12]. Furthermore, the knowledge about the long- term risk of IPMN developing in pancreatic cancer is contradictory. Crippa et al. reported an overall risk of 3.7% of IPMNs to develop into pancreatic cancer [13]. Choi et al. reported that a low risk IPMN (lesion without main pancreatic duct involvement or mural nodes) has a 7.8% chance after 10 years to progress into pancreatic cancer and a high-risk IPMN (mural nodes and dilatated main pancreatic duct) has 25% chance after 10 years to progress into pancreatic cancer [14].

In essence, the natural biologic history of most of the pancreatic cysts we treat today, is unclear. Therefore, we aim to establish the GERPACYST registry, a prospective, 20-year spanning, interdisciplinary, multicenter registry to structurally study the natural biology of different pancreatic cysts over time in order to build multidimensional models to calculate the individual’s risk for the development of malignancy.


### Study design

The GerPaCyst Study is a prospective, multicenter, interdisciplinary, longitudinal registry study. A formal protocol detailing aims and regulations for data safety and publication has been uploaded to https://drks.de/search/en/trial/DRKS00025927 and can be accessed publicly. This manuscript also provides a concise form to fulfill standards for documentation of registries and follows the Standard protocol items: recommendations for clinical trials (SPIRIT) guidelines [15].

### Participants, eligibility criteria and outcomes

Patients presenting at the respective participating centers including academic and academic-affiliated hospitals, with a presumed or confirmed pancreatic cyst (IPMN, MCN, SPPT, or SCN) will be evaluated for participating in the study. The diagnosis of a presumed pancreatic cysts will be established by the treating physician in accordance with the European evidence-based guidelines on pancreatic cystic neoplasms, the international, Sendai, Fukuoka criteria and the updated Kyoto guidelines [5,16–18], which defines the clinical, imaging and laboratory features required for case inclusion. Diagnosis criteria include the following:

Main-Duct IPMN is suspected for segmental or diffuse dilation of the main pancreatic duct (MPD) of >5 mm without other causes of obstruction.Any cyst above or equal 1 cm should be checked by CT or MRI with MRCP to check for high-risk stigmata, including enhanced solid component and main pancreatic duct size of more than 1 cm, or worrisome features”, including cyst over or equal 3 cm, thickened enhanced cyst walls, non-enhanced mural nodules, MPD size 5–9 mm, abrupt change in MPD caliber with distal pancreatic atrophy and lymphadenopathyAll cysts over 3 cms or with worrisome features or high-risk stigmata” should undergo EUS. MDCT and MRCP are most useful for distinguishing BD-IPMN from other cysts by showing multiplicity and a connection to the MPD. Cyst fluid is optional but can help to distinguish a BD-IPMN from a small oligocystic SCN with CEA determination.The distinction between main, mixed or branch-duct type IPMN should be made upon imaging. The pathological classification can only be done postoperatively.Neoplastic transformation will be separated into low-grade and high-grade dysplasia, as well as invasive cancer.MCN should be restricted to neoplasms exhibiting ovarian-type stroma.SPN/SPPTs are well-circumscribed mass with calcification, peripheral capsule, internal blood products, and lack of biliary/pancreatic ductal obstruction) on computed tomography and MRI are highly suggestive of the diagnosis of SPN, particularly when visualized in young female patients.

Imaging will be subjected to review at the University Medical Center Schleswig-Holstein, Campus Luebeck upon study inclusion for the prospective risk stratification model. For future research questions, MR and CT images will be reviewed at random to ensure quality of entered data. Discrepancies will be recorded and used to calculate inter-observer variability.

**These are the inclusion and exclusion criteria:**

**Inclusion criteria:**
Presumed pancreatic cyst of the following entities (IPMN, MCN, SPPT, SCN)At least 18 years old
**Exclusion criteria:**
Confirmed pseudocyst or diagnosis other than IPMN, MCN, SPPT, SCNLess than 18 years old

Suitable patients will be informed about the research project by the treating physician. The written informed consent will be obtained by each patient. The treatment interventions will not be altered by the study.

If the patient provides consent to participate in GerPaCyst, data entry will take place at the time of treatment initiation (surgery initiation of non-surgical surveillance) and every 6–12 months thereafter, for a period of up to 20 years. Participating centers complete an electronic Case Report Form (eCRF). Study data is collected and managed using REDCap electronic data capture tools hosted at the University of Luebeck, Germany [19,20] (Variables see S1 Table). Changes in patient characteristics are entered during patient follow-up. In addition, patient biobank samples (blood, cyst fluid, urine, tissue) will be stored upon availability.

The primary outcome of this trial is the development of high-grade dysplasia/invasive cancer during follow-up or the absence of it. The secondary outcomes are death, quality of life measured by EQ-5D-5L questionnaire, end-of-follow up and perioperative characteristics if applicable such as complications, length of hospital stay and clavien-dindo classification.

### Initiation algorithm

The study is still welcoming new participating centers from all over the world. Interested centers can contact: [contact] or [contact]. Once the study protocol has been reviewed by the ethics committee of the new center, and the contract has been approved by both legal departments, the participating physicians will receive proper training for patient inclusion in the REDCap based database.

### Participant timelines and follow-up schedules

Only after the patient has given written informed consent may the treating physician register the patient in the database. After patient registration, mandatory baseline data on premedical history, data on the disease, imaging and diagnostic modalities, treatment, and treatment outcome (e.g., post-op complications) are documented. In addition, the date of treatment initiation, patient number, and basic patient-specific information are documented (e.g., gender or month and year of birth). The study’s non-interventional design does not regulate modalities or intervals between examinations and thus does not intervene in routine clinical practice. Patients will be followed when presenting to the participating institutions or by telephone interview every 6–12 months. A detailed patient schedule is shown (Fig 1).

**Fig 1 pone.0335809.g001:**
[figure not shown]
SPIRIT schedule of enrollment, interventions, and assessment.

### Patient rights and data safety

Written informed consent for participation in the registry is obtained prior to inclusion at every center from all patients. Patient data are entered and stored in pseudonymized form. Institutional review boards have been obtained from every participating center. A data safety manual can be obtained from the senior author ([name]). The GerPaCyst platform was initiated and enabled for data collection in pancreatic cysts in 2021 (Ethics Committee of the University of Lübeck Az. 20−225 and 2024–265_1).

